### Participant recruitment

Potential participants will be identified by clinicians following presentation to emergency departments (EDs) or acute assessment units, through review of acute cervical spine CT reports, acute hospital attendance or through referrals or admissions to spinal services in the UK. An anonymised screening log will be kept.

Any neck stabilisation can be applied as part of standard care prior to randomisation, including; trauma collar, blocks, spinal board, padded hard collar (eg, Miami J, Aspen, Philadelphia) or soft collar. Standard care treatment, such as removal from spinal boards and placement of a padded hard collar will occur as usual, and will not be delayed by trial assessment and participation.

Eligibility assessment and randomisation will take place as soon as possible after injury (target within 48 hours) to maximise the impact of study intervention. However, falls in older and frail people are usually multifactorial,^25 26^ and conditions leading to the fall or resulting from the fall may affect capacity and fitness to participate. Recruitment can occur up to 3 weeks after the injury to provide flexibility for those presenting late, facilitate participation in those who are acutely unwell, and ensure time for involvement of patient representatives where needed.

The nested qualitative study will include healthcare professionals involved in patient recruitment, study participants, carers of participants lacking capacity and those who decline trial participation.

### Randomisation and interventions

Web-based randomisation will occur with a minimisation algorithm based on:

Age at randomisation (<75 vs ≥75 years).Odontoid fracture type (I–III).^24^Frailty (CFS ≥5 vs <5).^23^

The first participant will be allocated to one arm with a probability of 0.5 and subsequent participants will be allocated with a probability of 0.8 to the group which minimises differences of the above variables between the two trial arms. Treatment allocation will be disclosed to the local research team via the web interface following randomisation.

The standard care arm will involve 12 weeks of hard collar treatment, following local usual choice of hard collar and local usual arrangements for collar care. For those allocated to the intervention (collar removal) arm, the collar will be removed as soon as possible, but may be weaned over several days if required for optimising analgesia. Removal of a collar prior to 12 weeks in the hard collar arm or wearing of a collar in the no collar arm will be recorded as a failure of adherence with explanation. Soft collars will not be used in either arm.

### Outcome measures

The primary outcome measure is the EQ-5D-5L at 12 weeks postrandomisation.

Secondary outcome measures are:

Two and 6 weeks: EQ-5D-5L, Neck Disability Index (NDI), Neck Numeric Pain Scale.Twekve weeks: NDI, Neck Numeric Pain Scale, adverse events (AEs), compliance with hard collar use, analgesia use, length of hospital stay, discharge destination, bony fusion/stability on imaging, loss of muscle bulk in upper limbs using grip strength and bioimpedence.Six and 12 months: EQ-5D-5L, NDI, Neck Numeric Pain Scale, injury-related complications, mortality, health and social care visits/use, hospital admission or outpatient visits, health economics analysis.

### Trial assessments

Assessments and timing of data collection are shown in table 1. Baseline data on demographics, comorbidities, injury, radiological findings and inpatient management will be recorded. Patient diaries will be used to collect pain scores, analgesia and collar use. Standard local clinical follow-up will occur. Research assessments will be carried out at 2, 6 and 12 weeks by the local research team and by a blinded member of the central research team at 6 and 12 months. Assessments will occur via telephone interviews, postal or online questionnaires, or during standard care appointments. A proxy can provide information on a patient’s behalf when required. Up to three reminder telephone calls will be made to maximise completion.

**Table 1 T1:** Timing of study assessments

	Timing from randomisation						
	Baseline	Discharge	2 weeks	6 weeks	12 weeks	6 months	12 months
Assessment							
Eligibility assessment	*						
Consent	*						
Demographics							
Baseline data	*						
CFS^23^	*						
Imaging							
Fracture type	X						
Imaging type	X				X		
Outcomes							
EQ-5D-5L			*	*	*	*	*
EQ-VAS			*	*	*	*	*
Neck Numeric Pain Scale			*	*	*	*	*
NDI			*	*	*	*	*
AEs		*			*		
Injury-related complications						*	*
Collar use		*	*	*	*		
Grip strength/bioimpedance	*				*		
Service use			*	*	*	*	*
Analgesia use			*	*	*		
Mortality					*	*	*

Assessments undertaken as standard care are shown with x. Study specific assessments are shown with*. Assessments may occur within the following time windows: 2 weeks (±1 week), 6 and 12 weeks (±2 weeks) and 6 and 12 months (±4 weeks). Fracture type refers to that of Anderson and D’Alonzo.^24^

EQ-5D-5L - EuroQol 5 dimension instrument 5 level version

AEs, adverse events; CFS, Clinical Frailty Scale; NDI, Neck Disability Index; VAS, Visual Analogue Scale.

At centres with facilities for routine assessment of grip strength and bioimpedence, all participants will be invited to take part in this arm of the study. Loss of muscle bulk in the upper limbs will be assessed over 12 weeks using hand grip strength measured with a dynamometer.^27^ Bioimpedence measurements will be made at the wrist and ankle. Muscle mass and skeletal muscle index as a marker of frailty will be calculated as per Janssen *et al.*^28^

Approximately 25 patients in the collar arm will use temperature sensors to assess compliance with the collar (Thermochron iButtons).^29^ These will be the first participants willing to participate at centres where the temperature sensors can be missioned. Long-term follow-up of mortality and hospital admissions using anonymised data without participant contact will occur for 5 years.

No study specific follow-up imaging is mandatory. Participants will follow local clinical protocols for imaging. The modality and findings of all imaging undertaken will be recorded and imaging collected at the study centre for analysis where patient consent for transfer is given.

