## Introduction

### Background and rationale

Odontoid process (dens) fractures occur following low impact falls in frail and older people, and are increasing in incidence as the population ages.^1–3^ The Trauma Audit and Research Network database identified at least 1700 odontoid fractures each year in England and Wales, 85% in people over 65 years. One-year mortality following an odontoid fracture is 20%–50%, similar to or higher than following a hip fracture, likely reflecting the underlying frailty and health status of those at risk of low impact falls.^4–7^

In the UK, 85%–90% of frail or older people with a new odontoid fracture are managed non-operatively, most with 6–12 weeks immobilisation in a hard collar.^8–10^ This aims to promote bony fusion and prevent neurological deterioration or instability pain.^1 5 11^ However, hard collars only restrict 40%–50% of neck movements,^12 13^ and bony fusion rates of 20%–80% are variable across fracture types, management, age and frailty.^1 5 11 14–18^ Further, bony fusion may not be associated with pain, quality of life (QoL), mortality or functional outcomes in older people,^8 19 20^ and late neurological deterioration is very rare.^5 11 21^ Hard collars can cause skin pressure ulcers and difficulties with swallowing, breathing and personal care, all of which can affect QoL.^10 22^ Additional health and social care input is often required to assist patients with activities of daily living. If fibrous union, or lack of bony fusion is an acceptable outcome and hard collars can negatively impact QoL, then management of an odontoid fracture with a hard collar may be causing unnecessary harm and negatively impacting on QoL in a group for whom the short to medium term QoL may be more important than long term outcomes.

Spinal surgeons responding to a UK survey variably reported managing odontoid fractures without any immobilisation or removing hard collars in frail or older patients who were unable to tolerate a collar, had a short life expectancy or suffered complications.^10^ Ninety percent supported randomisation to management with or without a collar to determine optimum treatment.^10^ Further, feedback from patients managed in collars supports exploring whether collars are necessary for odontoid process fractures.

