### Safety considerations

AEs will be recorded up to 12 weeks. Expected AEs relating to hard collar use or odontoid process fractures include skin pressure ulcers, dysphagia and recurrent falls. All AEs (expected or not) will be reviewed by the local principal investigator and reported to the data monitoring committee (DMC). Serious AEs (SAEs) will also be reported to the trial sponsor, who will notify the REC. Outcome data, AEs and SAEs, will be routinely reviewed by the DMC. The DMC is independent and oversees trial safety and data monitoring. If the DMC assesses that the risk-benefit balance is significantly changed by any new safety information, amendments to the trial will be made.

The trial funder (NIHR) and cosponsors (University of Edinburgh and NHS Lothian) did not influence trial design. The sponsor ensures that data collection, management and trial monitoring are conducted appropriately and has overall responsibility for the study. Neither the funder nor the sponsor will have ultimate authority over writing of the report or the decision to submit the report for publication.

The trial will be coordinated by the central trial team based at the Edinburgh Clinical Trials Unit (ECTU), overseen by a Trial Management Group consisting of key trial members. Regular reports will be made to the Trial Steering Committee.

The protocol has been designed by the chief investigator and collaborators. The University of Edinburgh has insurance for negligent harm caused by poor protocol design, and participating sites have their own insurance and NHS indemnity for clinical negligence and other negligent harm.

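### Adverse events are scheduled for collection only at discharge and 12 weeks, although the local team already assesses participants at 2 and 6 weeks

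*Protocol article*

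**What the plan says.** Three places in the protocol article bear on AE timing, and they agree with one another.

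- **Trial assessments, Table 1.** The AE row is marked at discharge and at 12 weeks, and nowhere else. The 2- and 6-week columns are marked for EQ-5D-5L, EQ-VAS, neck pain, Neck Disability Index, collar use, service use and analgesia use.
- **Outcome measures.** AEs are a secondary outcome in the 12-week list. They are absent from the 2- and 6-week list.
- **Safety considerations.** "AEs will be recorded up to 12 weeks". All AEs are reviewed by the local principal investigator and passed to the data monitoring committee (DMC). Serious AEs also go to the sponsor. "Expected AEs relating to hard collar use or odontoid process fractures include skin pressure ulcers, dysphagia and recurrent falls".

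On contact and data sources, Trial assessments says: "Research assessments will be carried out at 2, 6 and 12 weeks by the local research team". It also says: "Patient diaries will be used to collect pain scores, analgesia and collar use". AEs are not named among the diary items. On who may answer: "A proxy can provide information on a patient’s behalf when required". The visit windows are ±1 week at 2 weeks and ±2 weeks at 6 and 12 weeks.

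**The concern.** Harm from hard collars is a large part of the reason for the trial, and the absence of harm from leaving the collar off is the other side of the same question. The AE comparison is the direct evidence on both. The events named as expected are ones that can begin and end between two widely spaced enquiries, in a population that includes people without capacity and answers given by proxies.

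The first AE time point is also not a fixed time. Discharge happens after randomisation, and length of stay is itself an outcome. If length of stay differs by arm, so does the period that the 12-week enquiry has to cover. The trial is unblinded, and only the collar arm has arrangements for collar care, so events noticed outside a scheduled enquiry may not be noticed equally in the two arms.

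At stake are under-counting of AEs that arise after discharge and, possibly, a distorted comparison between arms.

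**Working it through.** The article gives no figure for AE capture to reproduce. The check is on the interval between scheduled enquiries.

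**Inputs.** AE enquiries at discharge and 12 weeks (Table 1). Existing local assessments at 2, 6 and 12 weeks (Trial assessments). Windows: 2 weeks ±1, and 6 and 12 weeks ±2 (Table 1 footnote). Length of stay is not given, so the week of discharge, d, is varied.

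**Current schedule.** Gap after discharge = 12 − d nominally, and 14 − d if the 12-week assessment falls at the end of its window.

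| Discharge week d | Nominal gap (weeks) | Latest gap (weeks) |
|---|---|---|
| 0 | 12 | 14 |
| 1 | 11 | 13 |
| 2 | 10 | 12 |
| 4 | 8 | 10 |

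The maximum of about 12 weeks (14 at the window edge) therefore applies to those discharged close to randomisation, and longer stays shorten it. The look-back also moves one for one with discharge: a participant discharged at week 1 has an 11-week look-back, and one discharged at week 4 has 8 weeks. Any difference in length of stay between arms carries straight into the period covered.

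**With AEs added at 2 and 6 weeks.** For d = 0, the nominal gaps are 2 − 0 = 2, 6 − 2 = 4 and 12 − 6 = 6 weeks. The longest falls from 12 to 6. At the window extremes, the longest gap runs from an early 6-week assessment (week 4) to a late 12-week assessment (week 14): 14 − 4 = 10 weeks, against 14 now.

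**Participants who do not reach 12 weeks.** Under Table 1, someone who is discharged and then dies or is lost before the 12-week assessment has no scheduled AE enquiry after discharge. With the added time points, those who complete the 2- or 6-week assessment would have one or two.

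**Sample size.** The target of 887 is not affected by this point.

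**The case against.** The strongest reply is that Table 1 may show only when forms are completed. Safety considerations describes recording up to 12 weeks with investigator and DMC review, which is compatible with continuous reporting between assessments. Standard clinical follow-up also continues. Service use and collar use are asked at 2 and 6 weeks, and departures from the allocated arm are recorded with an explanation. Harms serious enough to need care or to change collar use thus have other routes into the data. The full protocol, which is not shown, may say how AEs are ascertained.

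Much of this stands, and it rules out several stronger readings that a reader might infer:

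- **That post-discharge AEs rest on recall.** The article does not state whether the source is recall, notes or ongoing reporting.
- **That AEs are lost in those who die.** AEs up to discharge have their own collection point, serious AEs have a separate route, and a proxy may answer. Nothing says that the 12-week form cannot be completed after a death.
- **That the number affected can be read from mortality.** Taking the Background's one-year mortality of 20% to 50% and assuming a constant hazard, 1 − 0.80^(12/52) = 5.0% and 1 − 0.50^(12/52) = 14.8%, or about 45 to 131 of 887 dead by 12 weeks. That counts all deaths, including those in hospital, who have no post-discharge gap, and early hazard may not be constant. It does not measure the number exposed to the gap.
- **That the DMC learns of events up to 14 weeks late.** This presumes that events surface only at the 12-week assessment, which the article does not say.
- **That harms present before randomisation will be counted as AEs.** The article does not itemise the baseline form or define when an AE starts. It is reasonable for an article to leave such definitions to the full protocol.

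The reply does not remove the schedule itself. The two AE time points are stated in Table 1 and match the outcome list. General wording on recording and review names no enquiry between discharge and 12 weeks.

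**Conclusion.** The point holds as a weakness in the stated schedule. It is not an error or a contradiction. The gap between scheduled AE enquiries can reach about 12 weeks, 14 at the window edge, for participants discharged early. After discharge, non-serious AEs have no scheduled enquiry in those who die or are lost before 12 weeks. A listed secondary safety outcome may be under-captured, and possibly unevenly, because discharge timing may differ by arm and the trial is unblinded.

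The gap lengths rest only on Table 1 and its windows. That events will be missed rests on the assumption that reporting between enquiries is incomplete, which the article neither confirms nor excludes. Neither the amount of under-capture nor the direction of any imbalance can be derived from the document. The change is worth making because it is cheap, not because a bias of known size has been shown.

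**What to change.** In Table 1, mark AEs at 2 and 6 weeks as well as at discharge and 12 weeks, and add AEs to the 2- and 6-week entry under Outcome measures. Ask the same AE questions in both arms, whichever of the existing modes is used (telephone, post, online or clinic) and whether the participant or a proxy answers.

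The cost is a few more questions and slightly longer 2- and 6-week assessments, with a small amendment to the forms. No new visits are needed.

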## Methods and analysis

### Study design

This manuscript has been prepared in accordance with the SPIRIT checklist. The DENS trial is a non-blinded randomised controlled trial with a nested qualitative study comparing early hard collar removal (intervention) with treatment in a hard collar for 12 weeks (standard care) in older or frail adults with a new odontoid process fracture. Figure 1 shows the trial flow chart. The study will recruit from November 2021 to December 2023.

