### Data analysis plan

The primary data analysis will be by intention to treat. A 5% two-sided significance level will be used throughout. A detailed statistical analysis plan will be developed by the study statisticians and finalised prior to locking of the trial database.

Analysis of the primary outcome will be a repeated measures analysis of covariance, including terms for treatment arm and the EQ-5D-5L responses at 2, 6 and 12 weeks. Adjustments will be made for the variables included in the randomisation minimisation algorithm. Adjustment for study site will be included as a random effect, if appropriate. The repeated measures approach enables estimation of an intervention effect at week 12 postrandomisation (primary outcome), and an overall assessment of the effect of the intervention over the 12-week period.

The 12-week NDI and Visual Analogue Scale will be analysed in a similar manner to the EQ-5D-5L. It is anticipated that results will underpin any between group differences seen in EQ-5D-5L, confirming and strengthening the clinical interpretation of the findings. All other secondary outcomes will be analysed with statistical models appropriate to the distribution of the outcome (see table 3). Where there are data recorded on multiple occasions postrandomisation, we may use an appropriate repeated measures model. Exploratory subgroup analyses by fracture type (I, II and III),^24^ CFS (<5 vs ≥5)^23^ and age (<75 vs ≥75 years) will be performed. The influence of any missing data on the robustness of the findings will be examined, for example, using multiple imputation models under a missing at random assumption. Screening logs will be analysed to assess generalisability of results.

**Table 3 T3:** Possible methods of analysis

Variable	Hypothesis	Outcome measures	Analysis methods
Baseline data	No difference between groups	Gender, age, comorbidities, injury data, radiological findings, inpatient management, CFS	Categorical variables: absolute numbers and percentages. Continuous variables: mean, median, SD, IQR.
Primary outcome			
Health-related quality of life at 12 weeks	Clinically important difference between two groups with early collar removal superior	EQ-5D-5L (continuous)	Repeated measures analysis of covariance at 2, 6 and 12 weeks, adjusting for minimisation variables
Secondary outcomes			
Pain	No difference between groups	NPRS (ordinal)	Ordinal regression

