### Participant capacity and consent

The study member obtaining consent will explain and clarify all relevant information, either face to face, or via telephone or video call, and give patients the time they need to decide whether to participate. Informed consent will be signed and dated by participants or their representative, and a study team member. Verbal consent from a participant or their representative, signed and witnessed by a study team member will also be valid. Participants may withdraw consent at any time without reason, without affecting their care.

Patients diagnosed with odontoid fractures may lack capacity. Recruitment of these patients is necessary to aid generalisability of the trial outcome and to allow equal access to any benefits of participation. All consent procedures will adhere to the Adults with Incapacity (Scotland) Act 2000, the 2005 Mental Capacity Act, the Mental Capacity Act (Northern Ireland) 2016 and their codes of practice. For patients in Scotland who lack capacity, the patient’s nearest relative, welfare attorney or guardian can provide consent. For patients in England, Wales and Northern Ireland who lack capacity, a personal consultee (relative or close friend) can provide consent. Where possible this will be written and signed, otherwise clear documentation of the discussion and named persons involved will be accepted.

If a participant without capacity regains capacity, informed consent will be sought to continue in the trial. In Scotland, if a participant has given informed consent, but loses capacity, they will remain in the study. In England, Wales, and Northern Ireland, if a participant has already given informed consent, but loses capacity, they will remain in the study only if consent is then given by a consultee.

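### Proxy answers are allowed in a non-blinded trial that enrols people lacking capacity, but the stated models and subgroups have no term for capacity at entry, which costs some precision and leaves no stated check on proxy error

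*Protocol article*

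**What the plan says.** **Who is enrolled.** The section on participant capacity and consent states "Patients diagnosed with odontoid fractures may lack capacity" and treats their recruitment as necessary for generalisability. Consent then comes from a representative or consultee. The section foresees change in both directions: "If a participant without capacity regains capacity, informed consent will be sought to continue in the trial", and there are separate rules for participants who lose capacity after consenting.

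**Who answers.** Under Trial assessments, "A proxy can provide information on a patient’s behalf when required". The sentence sets no limit by instrument or visit. It names no instrument either, but it stands in the paragraph on research assessments. Table 1 lists EQ-5D-5L, EQ-VAS, neck pain and NDI at every follow-up visit. None of these is collected at baseline.

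**Who knows the allocation.** "The DENS trial is a non-blinded randomised controlled trial with a nested qualitative study". "Treatment allocation will be disclosed to the local research team via the web interface following randomisation", and "Research assessments will be carried out at 2, 6 and 12 weeks by the local research team". A blinded central assessor takes over only at 6 and 12 months.

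**How the outcome is analysed.** "The primary outcome measure is the EQ-5D-5L at 12 weeks postrandomisation". The model is a repeated measures analysis of covariance over 2, 6 and 12 weeks, and "Adjustments will be made for the variables included in the randomisation minimisation algorithm". Those variables are age, fracture type and CFS; site may enter as a random effect. NDI and EQ-VAS follow the same approach, and Table 3 gives ordinal regression for pain. The subgroups are fracture type, CFS and age. Neither capacity nor respondent type appears in the minimisation, the model or the subgroups.

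**The concern.** A proxy's rating of another person's pain and quality of life is not the same measurement as that person's own report. What a wearer feels in the collar is part of the effect the trial wants to measure. An onlooker's impression of a visible collar is not. If the proxy error is the same size in both arms, it cancels. If it depends on whether a collar is seen, it enters the treatment difference directly.

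Two things are at stake. The first is precision. Capacity at entry is a baseline variable that probably predicts the outcome, and it is worth more here because there is no baseline EQ-5D-5L to adjust for. The second is interpretation. Under the stated plan, a reader of the result could not tell whether it depends on the participants for whom proxies are most likely to have answered.

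**Working it through.** **1. The plan's own figure.** For a difference of 0.05, SD 0.3, two-sided 5% and 90% power, the t-test needs 757 per arm, or 1514. Then 1514 / 0.8 = 1892.5, rounded up to 1893. Applying the two stated reductions, 1892.5 × 0.75 × 0.625 = 887.1. The target of 887 reproduces, so this point involves no arithmetic error.

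**2. Design standard error.** SE = 0.05 / (1.960 + 1.282) = 0.0154.

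**3. Precision forgone.** Let a share p lack capacity and score d lower. The share of variance explained is R² = p(1 − p)d² / 0.3². The SD is the article's; p and d are assumptions.
- p = 0.2, d = 0.1: 0.16 × 0.01 / 0.09 = 0.018.
- p = 0.4, d = 0.2: 0.24 × 0.04 / 0.09 = 0.107.

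This is 2–11% before overlap with CFS and age. The sample size already credits age and CFS with a correlation of 0.5, or 25% of variance, so the added gain may be smaller.

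**4. Proxy error equal in both arms.** There is no bias, only extra variance: SD′ = √(0.09 + p(1 − p)s²) for proxy share p and shift s. At the extreme of p = 0.4 and s = 0.2, SD′ = √0.0996 = 0.3156 and power is 86.9%. For p from 10% to 40% and s from 0.05 to 0.20, power stays at about 87–90%.

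**5. Proxy error that differs by arm.** Bias = proxy share × differential error. The article gives neither, so both are assumptions.

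| Proxy share | Differential error | Bias | Type I error | Power if bias opposes the effect |
|---|---|---|---|---|
| 10% | 0.02 | 0.002 | 5.2% | 87.5% |
| 20% | 0.05 | 0.01 | 9.9% | 73.7% |
| 40% | 0.10 | 0.04 | 73.7% | 9.5% |

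For the middle row, bias/SE = 0.01 / 0.0154 = 0.648. Type I error = P(Z > 1.960 − 0.648) + P(Z < −1.960 − 0.648) = 0.099. Power = Φ(0.04 / 0.0154 − 1.960) = 0.737.

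**6. What the proposed checks can show.** Take 20–40% lacking capacity, as in step 3.
- Restricting to capacity at entry gives an SE of 0.0154 / √0.8 = 0.017 to 0.0154 / √0.6 = 0.020.
- The capacity-by-arm interaction has SE = 0.0154 / √(p(1 − p)), which is 0.0154 / 0.40 = 0.039 to 0.0154 / 0.49 = 0.031.

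If proxies answered for exactly those lacking capacity at entry, a differential error of 0.05 would be only 1.3 to 1.6 interaction standard errors. The interaction should therefore be read as an estimate with its confidence interval; a non-significant test would not be reassurance.

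**The case against.** **This belongs to the analysis plan.** The article defers to a detailed analysis plan, and Table 3 calls its methods possible ones. A tick-box for respondent type and a rule to keep the same respondent are case-report-form or full-protocol detail; that objection stands, and the point does not rest on them. The covariate set and the subgroups, however, are stated in the article, so they can be questioned here. The unseen plan may already add a capacity term or a sensitivity analysis.

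**Pooling is inferred.** The article does not say outright that proxy and self-reports are analysed together. That follows from a single model with no respondent term. This stands as a caveat.

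**Randomisation already protects the comparison.** A reader might infer that omitting capacity biases the result. It does not: capacity at entry is balanced in expectation, and CFS is already in the model.

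**The direction is unknown.** A reader might infer that proxies mark down collar wearers and so favour collar removal. Nothing in the article supports that. A proxy could as easily see the collar as protective, or worry about a patient without one. Nor do proxies create the unblinding, since participants know their own allocation.

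**The serial correlation.** A reader might infer that a change of respondent between visits lowers the assumed 0.44 and so undermines the sample size. The stated 37.5% reduction matches 1 − (1 + 2 × 0.44)/3 = 0.373. Under that formula a lower correlation does not raise the required number. The article also plans a re-estimation on the first 300 participants.

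**A covariate cannot remove arm-differential error.** This is correct. A main effect of capacity serves precision only; the sensitivity analyses are what address proxy error.

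**Conclusion.** The point holds as a modest, inexpensive improvement to the stated analysis. It does not show that the primary comparison is biased. Omitting capacity at entry gives up an estimated 2–11% of variance before overlap with CFS and age. It also leaves no stated check on proxy error that differs by arm. At 20% proxies and a 0.05 differential error, such error would shift the estimate by 0.01, one fifth of the 0.05 target, and raise type I error to about 9.9%. All proxy shares, score gaps and capacity shares are assumptions, because the article gives none. Across the assumed range the bias runs from 0.002, which is negligible, to 0.04, which would be serious. The sample size of 887 is unaffected.

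**What to change.** 1. Add capacity at randomisation (consent by the participant versus by a representative or consultee) as a fixed covariate in the repeated measures models for EQ-5D-5L, NDI and EQ-VAS, and in the pain model.
2. Prespecify a sensitivity analysis of the primary outcome in participants with capacity at entry, and a capacity-by-arm interaction, each reported with a confidence interval.
3. Do not adjust the primary model for who answered after randomisation. That is decided after allocation and may be affected by it.

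Two limits should be stated with the results. The capacity-at-entry analysis does not catch proxies used for people who lose capacity later. An interaction may also reflect a real difference in effect and not only proxy error.

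The cost is one extra model parameter and two extra analyses. No new data are needed, because the consent route already records the variable.
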